### Strategies to improve adherence to intervention/comparator {15c}

There are two time points during the follow-up period where adherence to the intervention will be recorded. At 6–8 weeks and 11 months after randomisation, the site research team are to review the participant’s medical records to ensure that the participant has been allocated to the appropriate follow-up appointment type i.e. those allocated to PIFU have not been booked for a routine visit in 6–12 months. Should any errors be found, a member of the site research team will contact the relevant local team/person to correct the error.

A final adherence check will be done at the 24 month visit where the site research team are to review the participant’s medical records to ensure that the participant has been allocated to the appropriate intervention. If an error has been found, this will be recorded in the Case Report Form (CRF).

### Concomitant care permitted or prohibited during the trial {15d}

There are no concomitant care or interventions that are prohibited during the trial.

### Ancillary and post-trial care {34}

At the end of trial participation, follow-up in rheumatology will continue following standard practice of that centre. Participants will discuss with their clinical care team whether they wish to continue with standard follow-up or PIFU care. Insurance from the study sponsor (University of Oxford) covers any harm suffered by participants related to study participation.

### Outcomes {16}

A full list of primary, secondary and exploratory outcomes is given in Table 1. The primary outcome is the MSK-HQ at 24 months, with additional assessments throughout the 24-month study through remote data collection in both groups every 6 months via email, post or telephone. We feel that the most important outcome is the overall impact of PIFU on patients.

**Table 1 Tab1:** Primary and secondary outcome measures

Primary objective	Outcome measure	Time point(s) of evaluation of this outcome measure (if applicable)
To assess the effectiveness of PIFU compared to standard care on musculoskeletal quality of life at 24 months	MSK-HQ score	Baseline, months 6, 12, 18 and 24
**Secondary objectives**	**Outcome measure(s)**	**Time point(s) of evaluation of this outcome measure (if applicable)**
To assess the effectiveness of PIFU compared to standard care on musculoskeletal quality of life over 24 months	MSK-HQ score	Baseline, months 6, 12, 18, and 24
To assess the effectiveness of PIFU compared to standard care on musculoskeletal quality of life at 6, 12 and 18 months	MSK-HQ score	Baseline, months 6, 12, 18 and 24
To assess the effectiveness of PIFU compared to standard care on overall health related quality of life	EuroQol 5 Dimensions 5 Level Version (EQ-5D-5L) and EuroQol Visual Analogue Scale (EQ-VAS) scores	Baseline, months 12 and 24
To assess the incremental cost of PIFU compared to standard care	Incremental cost	Baseline, months 6, 12, 18 and 24
		12 months prior to Baseline through month 24
To assess the cost-effectiveness of PIFU compared to standard care	Cost per quality adjusted life year (QALY) gained	24-month time horizon
To compare the effect of PIFU versus standard care on progression from no treatment to first line DMARD	Proportion of patients starting a first line DMARD during the study	24 months
To compare the effect of PIFU versus standard care on progression from conventional drugs to biologic therapies	Proportion of patients starting a first biologic during the study	24 months
To compare the effect of PIFU versus standard care on disease activity	Clinical disease activity index (CDAI) and disease activity score (DAS28-CRP) for Rheumatoid Arthritis (RA) Ankylosing spondylitis disease activity score (ASDAS) for Axial Spondyloarthritis (AxSpA) Disease activity in psoriatic arthritis (DAPSA) for Psoriatic Arthritis (PsA)	Baseline and 24 months
To compare the effect of PIFU versus standard care on disease activity	Number of flares	Baseline and 24 months
To compare the effect of PIFU versus standard care on patient efficacy	Perceived efficacy in patient-physician interactions (PEPPI) score	Baseline and 24 months
To compare the effect of PIFU versus standard care on depression	Mental health using Patient Health Questionnaire-4 (PHQ-4)score	Baseline and 24 months
To evaluate the acceptability of PIFU to patients and health professionals/service providers	Semi-structured interviews	Weeks 2–12 and Months 16–24
		Once site has been open to recruitment for at least 12 months
**Exploratory objectives**	**Outcome measure**	**Time point(s) of evaluation of this outcome measure (if applicable)**
To explore potential risk factors, and their association with PIFU outcomes	MSK-HQ score	Baseline, months 6, 12, 18 and 24
	Disease activity score	24 months
To explore the reasons patients declined to participate in the TaILOR study	Online and/or paper brief survey designed by the team	During recruitment

We need to rely on a PRO that can be completed remotely as we believe that there is a risk that bringing patients in for a study visit during the two-year follow-up, may contaminate the PIFU approach, which is an issue with previous trials. Many PROs, such as the health assessment questionnaire (HAQ) were rejected by the patient partners as they were felt to be too outdated, only measuring significant levels of physical impairment rather than more subtle impacts of the disease.

The MSK-HQ is a patient-reported outcome assessing musculoskeletal Health Related Quality of Life (QoL) that has been validated in patients with inflammatory arthritis. The MSK-HQ was developed in 2016 by Arthritis Research UK to capture constructs specific to musculoskeletal health but designed for use across a range of rheumatological conditions and settings [16]. It incorporates measures of symptoms, e.g. pain and disease impact and was developed with significant patient input. Scores range from 0 to 56 with higher scores representing better musculoskeletal health. The MSK-HQ includes domains key to patients’ perception of musculoskeletal health, correlates highly with other PROs in inflammatory arthritis and has robust psychometric properties [17].

### Harms {17}

As PIFU is considered to be standard care within the NHS, safety reporting is not applicable for this study. Patient reported flare information (total number of flares as well as the number that required follow-up with a medical provider and steroid treatment) will be collected every 6 months and summarised and reviewed by the DMC.

Although no conventional biomedical adverse events are anticipated, we recognise the potential for inequitable distribution of benefits or unintended social harms associated with the intervention. To mitigate this risk, the study has been designed with a strong focus on inclusivity, including recruitment across diverse populations and settings, flexible participation options, multilingual materials, and ongoing monitoring of ethnicity and deprivation data. Recruitment patterns will be reviewed by the Trial Management Group (TMG) to identify under-representation of particular groups and implement targeted actions where required. These measures will also allow exploration of whether intervention uptake, engagement, or outcomes differ across population subgroups.

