## Abstract

**Background:**

Inflammatory arthritis comprises lifelong conditions, such as rheumatoid arthritis, axial spondyloarthritis and psoriatic arthritis that require long-term treatment and regular monitoring. People with inflammatory arthritis usually require long-term treatment with immune-suppressing medications and are typically reviewed in outpatient clinics every 6–12 months, accounting for 1.3 million appointments/year in the UK. The National Health Service (NHS) is implementing a move to patient-initiated follow-up (PIFU) where patients request appointments as required. To date, there are small studies of PIFU in rheumatoid arthritis and none in other arthritis. Research is required to configure services to optimise outcomes, inform patients and clinicians of the effectiveness and safety of PIFU and ensure that suitable patients are selected for this pathway.

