## Objectives {10}

The aim of the study is to assess the effectiveness and cost-effectiveness of PIFU compared to standard care in terms of musculoskeletal QoL outcomes for patients with inflammatory arthritis. We will also undertake qualitative work to gain insight into the barriers, facilitators and acceptability of PIFU from the perspective of patients and NHS professionals.

This study is part of a programme of work to establish whether and/or in which circumstances PIFU is superior to standard care for people with inflammatory arthritis. The data arising from this study will be used, along with data from a separate observation study on routine data undertaken as part of this programme, to investigate factors associated with better PIFU outcomes and to enable extrapolation of the trial results to the wider UK population.

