### Health economics

A within-trial economic evaluation will estimate the incremental cost and cost-effectiveness of PIFU compared with standard care from an NHS perspective. The base case analysis will take a 24-month time horizon. Data on NHS resource use over the 12 months before randomisation and the two-year study period will be obtained from participant questionnaires and hospital medical records. A sensitivity analysis will take a societal perspective and will also include costs incurred by patients, their families and employers. This will use data from patient-reported questionnaires on the cost of travelling to outpatient visits and time off work due to inflammatory arthritis.

To maximise statistical power and minimise patient burden, the analysis will focus on the medications, procedures, investigations and admissions that are most likely to drive the NHS cost difference between PIFU and standard care. Costing analyses will include the following resources: all outpatient consultations; all interactions with primary care professionals; accident and emergency consultations; DMARD medications for inflammatory arthritis; rheumatology advice lines; and procedures, investigations and admissions related to inflammatory arthritis disease process or treatments. The procedures, investigations and admissions related to inflammatory arthritis and treatment were prespecified in discussions between health economists and clinicians. This includes: relevant imaging such as musculoskeletal ultrasound; joint replacement; injection of intra-articular medications; and admissions for infection. Data on medications other than DMARDs will not be collected as they are not expected to have a material impact on incremental costs.

EQ-5D-5L will be used to estimate Quality Adjusted Life Years (QALYs); if no validated UK tariff is available, we will use the cross-walk tariff [28]. Cost-effectiveness will be expressed as incremental cost per QALY. Bootstrapping will be used to quantify uncertainty around costs, QALYs and cost-effectiveness ratios as 95% confidence intervals and cost-effectiveness acceptability curves. Analyses will adjust for covariates including demographics, costs in the 12 months before randomisation and baseline EQ-5D-5L. The economic evaluation will follow the National Institute for Health and Care Excellence (NICE) reference case [29] and Consolidated Health Economic Evaluation Reporting Standards (CHEERS) checklist [30].

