### Composition of the data monitoring committee, its role and reporting structure {28a}

An independent DMC was established for this study. The DMC will adopt a DAMOCLES-based charter, which defines its terms of reference and operation in relation to the oversight of the study. The DMC will meet regularly throughout the study at time-points agreed by the Chair of the Committee and the CI. At a minimum this will be on an annual basis. The DMC will review the patient reported flare data generated and make recommendations as to whether the protocol should be amended to protect patient safety. Recommendations of the DMC will be discussed between the CI, TSC, and the Sponsor.

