## Discussion

Inflammatory arthritis comprises lifelong conditions, such as RA, AxSpA and PsA that require long-term treatment and regular monitoring of disease and treatment. The implementation of PIFU where patients request appointments as required may offer an opportunity to empower patients, supporting self-management and a sense of control over healthcare decisions. It could improve patients’ experience of care and enable clinicians to focus their attention on those whose clinical need is greatest. However, there are concerns from patients and clinicians that PIFU should not compromise patients’ short-term or long-term outcomes, nor result in increased health inequalities and that PIFU should be tailored to the individual patient and the service concerned. To date, there are small studies of PIFU in RA and none in other arthritis. The research within the TaILOR programme of work is required to provide further data on PIFU across different forms of inflammatory arthritis in the UK. This can help to configure services to optimise outcomes, reassure patients and clinicians of the effectiveness and safety of PIFU and ensure that suitable patients are selected for this pathway.

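### Safety reporting is waived although PIFU is the randomised intervention, and serious events collected in both arms are designated only as costs, not summarised by arm as harms

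*Protocol article*

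**What the plan says.** All references are to the protocol article.

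- **Purpose.** The abstract's Background says research is needed to "inform patients and clinicians of the effectiveness and safety of PIFU". The Discussion says the programme can help to "reassure patients and clinicians of the effectiveness and safety of PIFU". Background and rationale {9a} calls the earlier rheumatology trials inconclusive on whether PIFU helps or harms, and records concern from patients and clinicians that it should not compromise outcomes.
- **Formal aim.** Objectives {10} is narrower: "The aim of the study is to assess the effectiveness and cost-effectiveness of PIFU compared to standard care". Safety is not named.
- **Harms {17}.** "As PIFU is considered to be standard care within the NHS, safety reporting is not applicable for this study". Patient-reported flares, including those needing medical follow-up and steroids, "will be collected every 6 months and summarised and reviewed by the DMC". The next paragraph begins "Although no conventional biomedical adverse events are anticipated" and turns to inequity and social harms.
- **DMC.** Section {28a}: "The DMC will review the patient reported flare data generated and make recommendations as to whether the protocol should be amended to protect patient safety". Interim analyses {28b} is wider. There the committee sees the accumulating confidential data and may recommend pausing or stopping for safety.
- **Resource use.** Health economics costs A&E consultations and "procedures, investigations and admissions related to inflammatory arthritis disease process or treatments", with admissions for infection and joint replacement given as examples.
- **Outcomes {16}.** Table 1 is presented as the full list. It has flares, disease activity, first DMARD, first biologic, PHQ-4, PEPPI, EQ-5D-5L and MSK-HQ. It has no admissions, A&E attendances or deaths.

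**The concern.** The reason given for the waiver is that PIFU already counts as standard NHS care. In this trial PIFU is the intervention under test. The comparator is itself called standard care, and its patients must not be moved to PIFU ({15a}). PIFU replaces booked reviews every 6 to 12 months with one booked appointment at month 24, in people who usually take immune-suppressing drugs. Being in routine use may justify dispensing with expedited reports of individual events. It does not justify leaving serious events uncompared between the arms.

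The cost analysis concentrates on resources expected to drive a difference between the arms, and infection admissions are among its examples. Such events are thus recorded for each arm but assigned no role as harms. An imbalance in them would have no designated place in the outcome list and would reach the reader mainly within a cost total. The trial would then have little to say on serious events, although the article presents safety as something the research should inform.

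**Working it through.** **1. The plan's own figure.** The point disputes no number, but the sample size fixes the precision available. With a difference of 4, SD 11.5, two-sided 5% and 90% power (Sample size {19}):

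n = 2 × (1.96 + 1.2816)² × 11.5² / 4² = 173.7, so 174 per arm by the normal approximation. The t-test gives 174.7, so 175 per arm, with power 0.90. Then 350 / 0.8 = 437.5, so 438. The stated figures reproduce.

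**2. Where each serious event appears.**

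| Event | Collected? | Role given | In Table 1? | Named for the DMC? |
|---|---|---|---|---|
| Patient-reported flares | 6, 12, 18, 24 months (Table 2) | Secondary outcome and harms monitoring | Yes | Yes ({17}, {28a}) |
| A&E consultations | Yes (Health economics) | Cost | No | Not by name |
| Infection- and arthritis- or treatment-related admissions | Yes (Health economics) | Cost | No | Not by name |
| Deaths | Not mentioned | None | No | No |

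The named flare data come from participants who know their allocation (Table 3).

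**3. Timing.** Table 2 schedules resource-use questionnaires at baseline and at 6, 12, 18 and 24 months, but the notes review for hospital resource use only at baseline and month 24. Participant timeline {18} likewise defers data on hospital appointments to month 24. The article does not say which source supplies which event. Before month 24 the DMC could see these events only as far as the questionnaires ask about them.

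**4. Precision of a comparison by arm.** The documents give no event rates, so the 24-month risks below are assumptions, with all 219 per arm analysed.

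Half-width of the 95% interval for a risk difference at equal risks p: 1.96 × √(2p(1−p)/219).

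- p = 2%: 1.96 × √(0.0392/219) = 2.6 percentage points
- p = 5%: 1.96 × √(0.095/219) = 4.1 points
- p = 10%: 1.96 × √(0.18/219) = 5.6 points

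Power for a doubling, with mean risk p̄: Φ{[(p₂−p₁) − 1.96√(2p̄(1−p̄)/219)] / √([p₁(1−p₁)+p₂(1−p₂)]/219)}.

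- 2% v 4%: Φ[(0.02 − 0.0320)/0.0163] = 23%
- 5% v 10%: Φ[(0.05 − 0.0493)/0.0251] = 51%
- 10% v 20%: Φ[(0.10 − 0.0669)/0.0338] = 84%

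Unless the events are common, a comparison would describe rather than test.

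**The case against.** The strongest defence has four parts.

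*The waiver may mean only individual-event reporting.* The sentence is followed at once by flare monitoring, so harms are not ignored. This is a fair reading, and it is why the remedy is one of wording. As written, though, the sentence waives safety reporting outright and for a reason that does not fit a randomised intervention.

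*The DMC is not confined to flares.* A reader might infer from {17} and {28a} that it sees nothing else. The documents do not support that. Section {28b} gives it the accumulating data, and Table 3 has statisticians and health economists producing closed reports. Flares are the only safety data named, which is a narrower point.

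*Disease-related harm is partly covered.* Disease activity (assessed blind where possible), treatment escalation, PHQ-4, EQ-5D-5L and MSK-HQ are compared by arm, so it would be wrong to say that safety rests on flare counts alone. These outcomes do not, however, capture infection admissions, emergency attendance or death.

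*Safety is not a formal objective, and other sources may contribute.* The Discussion's statement concerns the wider programme, which includes an observational study. NHS numbers are collected in England for possible further outcome data. The SAP, health economics plan and DMC charter are not shown and may add tables. All of this stands, but none of it corrects the Harms wording or the outcome list.

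A reader might also infer that Health economics contradicts Harms. It does not: costing admissions that occur in treated arthritis does not predict that PIFU causes them. The two sections are in tension only.

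**Conclusion.** The concern holds in a limited form and should be acted on. The article offers the research as informative on safety, declares safety reporting inapplicable for a reason that does not fit the intervention under test, and gives A&E attendances and relevant admissions no role except as costs. Deaths are not mentioned. Sections {17} and {28a} need reconciling with {28b} on what the DMC reviews.

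The size is qualitative: two classes of serious event collected in both arms, none compared as a harm, and one class (deaths) absent from the article. The primary analysis and the sample size are unaffected.

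A reader might infer that a doubling of serious events would be plain in the existing data. The documents give no rates to support this. Under the assumed risks, power for a doubling runs from 23% to 84%, and incomplete follow-up would lower it. The case for tabulating these events is transparency and oversight, not the prospect of a decisive test. The conclusion rests on the article as published; a fuller DMC charter or analysis plan could already supply some of the tables.

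**What to change.** 1. **Harms {17}.** Replace the statement that safety reporting is not applicable. Say instead that individual-event or expedited reporting is not required, but that harms will be summarised by randomised arm.
2. **Table 1.** Add a descriptive harms outcome, with counts, rates and 95% confidence intervals and no formal test. It should cover A&E attendances and infection- and arthritis- or treatment-related admissions, from the data already collected. Add deaths through one new field, for example at the month-24 notes review or on the withdrawal form.
3. **DMC {28a}.** Name these items alongside flares, as far as the 6-monthly questionnaires supply them, and align the text with {28b}.

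The cost is a few sentences, one data field and a few tables. Table 3 already gives statisticians and health economists access to allocations for closed reports. The drawbacks are imprecise estimates for rare events and recall error in self-reported items.

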### Participant timeline {18}

Regardless of the study arm, there are only two timepoints (baseline and month 24) at which hospital attendance is required for the purpose of the study. These are both routine care visits at which the relevant disease activity score will be determined (as part of routine care) or extracted from the participant’s medical notes; these assessments may be performed by study investigators or by a member of the rheumatology care team. All other data collection is via questionnaires completed directly by the participants during the baseline visit or completed by participants remotely. Data on hospital appointments attended between the baseline and month 24 study visits will be captured at the month 24 visit and do not need reporting at the time of the visit. As standard care and PIFU follow-up pathways may vary depending on Trust specific guidelines, participants will be provided with site-specific instructions on how to contact their care team if required. This may be their rheumatology clinical care team or the MDT at the hospital or secondary care site. Therefore, patients allocated to the standard care arm should attend any routine appointment during the study period and patients allocated to the PIFU arm should attend any PIFU appointments required during the study period. Any routine care assessment or tests that are determined to be required during any clinic appointment should be performed as medically indicated. These appointments (outside of baseline and month 24 visits) are not study visits (Fig. 1).

